### Study population and sample size

CKD Patients on hemodialysis for more than 3 months, aged over 18 years old, who gave their consent will be included (Table 2).

**Table 2 Tab2:** Inclusion, non-inclusion, and drop-out criteria

Inclusion criteria: - Under hemodialysis for more than 3 months - Aged over 18 years old - Gave their consent	
Non-inclusion criteria: - Non-fluent French speaker - Incapacity to provide consent or to answer questionnaires - Pregnancy or breast feeding - Cognitive impairment - Bedridden or life expectancy <1 year - Active cancer - Uncontrolled hyperparathyroidism as defined by the K-DIGO (iPTH >9x normal laboratory maximal value), cinacalcet treatment or hypocalcemia <2.0 mmol/L or hypercalcemia >2.7mmol/L - Past osteoporosis fracture - Treatment with active vitamin D - Unable to perform handgrip measurement - 25OHD >50nmol/L without vitamin D treatment - Cholecalciferol intolerance or allergy	
Drop out criteria: - 25OHD >50nmol/L after 12 months wash-out - Hypercalcemia >2.7mmol/L - Hyperparathyroidism (iPTH >9x normal laboratory maximal value) during wash-out or after randomization if patient is in the no treatment group - Hypoparathyroidism (iPTH <3x normal laboratory lower value) in a patient receiving cholecalciferol - Cholecalciferol intolerance or allergy - Death, renal transplantation - Pregnancy - Consent withdrawal - Renal recuperation allowing hemodialysis to stop - Unability to perform handgrip	

Inclusion, non-inclusion and drop-out criteria are described in Table 2. Hyperparathyroidism was defined as the Kidney Disease Improving Global Outcome (KDIGO) by an iPTH level >9 times the upper normal limit of the assay [64].

Sample size was calculated in order to meet our main objective and based on an observational study showing a dose-dependent correlation between 25OHD and muscle strength measured by handgrip [15]. In this study, mean muscle strength was 13 ± 8 kg in patients with 25OHD < 50 nmol/L and 18 ± 8 kg in patients with 25OHD > 75 nmol/L. To show a 5-kg difference between the two groups, considering a standard deviation of 8 kg, an α-risk of 0.05, and a power of 0.9, the number of patients required is 54 patients in each group (*t* test comparison of 2 independent means, https://marne.u707.jussieu.fr/biostatgv/). The study will continue until 110 patients will reach the end of the study according to the protocol.

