### Statistical analysis

A flow-chart diagram will describe the number of patients by status (inclusion, drop-out, randomization, follow-up). Patient characteristics will be described by treatment groups: qualitative data will be expressed as number and percentages, and quantitative data as mean and 95% confidence interval. Comparison between the two groups will be performed using the Chi-2 test for qualitative variables and the Student test for quantitative variables. If conditions to use these tests are not met, comparisons will be performed using appropriate non-parametric tests (Fischer’s exact test, Mann-Whitney test). Analyses will be considered as significant if *p* value is ≤ 0.05, in a bilateral situation.

The main objective will be analyzed by comparing muscle strength variation during the treatment period (M0–M6) between treated (receiving cholecalciferol) and non-treated group using a covariance analysis in which principal analyzed effect will be the treatment group and will be included as covariables the initial muscle strength, the study center, age stratification (< or ≥ 70 years old), and gender. Principal analysis will be based on intention to treat principle.

Secondary analyses will compare the ADL, FIND, and KDQOL scores between the two treatment groups using the same statistical method (analysis of covariance). The decreased of 25OHD plasma level will be described at the end of the wash-out period (mean change from inclusion and number of patients with 25OHD ≤ 50 nmol/l). To analyze factors associated with 25OHD lowering speed, a linear (or the most appropriate function) mixed model (random intercept and/or slope) will be performed including variables potentially related to 25OHD changes, such as but not limited to age, gender, BMI, diabetes, and duration of previous 25OHD treatment.

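### Drop-out rules that differ by arm after randomisation, and a target counted in protocol completers, put the intention-to-treat analysis at risk unless M6 handgrip is still measured after a trigger

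*Protocol article*

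**What the plan says.** All references are to the protocol article.

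- **Drop-out rules (Table 2, Study population and sample size).** iPTH above 9 times the upper normal value is a drop-out criterion "during wash-out or after randomization if patient is in the no treatment group". The low-side criterion is "Hypoparathyroidism (iPTH <3x normal laboratory lower value) in a patient receiving cholecalciferol". Both stand in one list with death, transplantation and consent withdrawal. The non-inclusion criteria in the same table cover high iPTH but not low iPTH.
- **Recruitment target (same section).** "The study will continue until 110 patients will reach the end of the study according to the protocol". The Discussion repeats that the aim was enough patients who end the study as the protocol expects.
- **Primary analysis (Statistical analysis).** The M0–M6 change in handgrip is compared by ANCOVA, adjusted for initial strength, centre, age stratum and gender. "Principal analysis will be based on intention to treat principle".
- **Timing (Table 1; Biological dosing).** Handgrip and iPTH are both scheduled at M0, M3 and M6, and the three-monthly laboratory values are used to look for drop-out criteria.

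**The concern.** After randomisation the two arms are filtered at opposite ends of iPTH, a variable that the study treatment can itself move. A patient whose iPTH is already low at M0 meets a drop-out criterion if allocated to cholecalciferol and does not if allocated to control, so allocation alone decides whether the rule applies. Intolerance of cholecalciferol carries no arm-specific wording, but in practice it can arise only in the treated arm.

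The target counts only patients who finish as the protocol prescribes, so each drop-out is made good by further recruitment. Power is protected in this way, but comparability is not. If patients who meet a trigger have no M6 reading, the M0–M6 change exists only for completers, and randomisation no longer guarantees that the completers of the two arms are alike.

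**Working it through.** **1. The plan's own figure.** Inputs from Study population and sample size: "To show a 5-kg difference between the two groups", "considering a standard deviation of 8 kg", "an α-risk of 0.05", power 0.9. The Statistical analysis section makes the test two-sided ("value is ≤ 0.05, in a bilateral situation").

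n per group = 2 × (1.960 + 1.282)² × 8² / 5² = 53.8, which rounds up to 54. This reproduces the stated 54 per group, 108 in total. The noncentral t calculation gives 54.8, so 55 per group or 110 in total. At 55 per group, power is 90.1% by the t calculation. The arithmetic is sound, and 110 completers deliver the planned power.

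**2. What counting completers implies.** The article gives no drop-out rate. For an assumed loss d, the number randomised is 110 / (1 − d):

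| Assumed loss | Randomised | Not completing |
|---|---|---|
| 10% | 123 | 13 |
| 20% | 138 | 28 |
| 30% | 158 | 48 |

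So 13 to 48 randomised patients could lack an M6 value if drop-outs are not measured.

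**3. Would those patients be measured?** The passages side by side:

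- The first item in the drop-out list, 25OHD still high after 12 months of wash-out, is described under Study design as exclusion from the study.
- The flow chart in Statistical analysis treats drop-out and follow-up as separate statuses.
- Table 1 has no visit for a patient who has met a drop-out criterion.
- Against this, intention to treat is stated without qualification, and no sentence says that measurement stops.

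The text leans towards leaving the study but does not settle the matter.

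**4. Size of bias if they are not measured.** Assume a true effect of zero, a fraction q removed from opposite iPTH tails in the two arms, and correlation ρ between iPTH and grip change. Let c be the normal quantile at 1 − q and φ the normal density. The mean iPTH of those retained shifts by λ = φ(c) / (1 − q) standard deviations. The two arms shift in opposite directions, so the shifts add: bias = 2 × ρ × λ × SD.

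| q per arm | λ | ρ = 0.2, SD 8 kg | ρ = 0.3, SD 8 kg |
|---|---|---|---|
| 5% | 0.109 | 0.35 kg | 0.52 kg |
| 10% | 0.195 | 0.62 kg | 0.94 kg |
| 15% | 0.274 | 0.88 kg | 1.32 kg |

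Example: 2 × 0.2 × 0.195 × 8 = 0.62 kg.

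Simulation with 55 completers per arm agrees. It gives a type I error of 5.5% and 6.2% in the first row, 7.4% and 9.3% in the second, and 8.6% and 14.0% in the third. With ρ = 0 there is no bias and the error stays at about 5%.

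The 8 kg is the SD of strength levels in the observational study cited for the sample size. The SD of a change may be smaller. At 4 kg the biases halve, to 0.17–0.66 kg. The type I error does not change with the SD, because bias and standard error scale together.

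**The case against.** A reader might infer that these rules turn the stated analysis into a completers' comparison, or that intention to treat cannot be carried out on the data this plan collects. The documents do not support that.

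- The 110 sentence fixes when recruitment stops, not who is analysed. More patients can be randomised and all of them analysed.
- No passage removes drop-outs from the analysis, defines a completers' set, or says that handgrip ceases after a trigger. This is a journal article, and the full protocol or the analysis plan may deal with follow-up and missing M6 values.
- iPTH and handgrip are scheduled at the same visits. A trigger found at M6 coincides with an M6 reading, and a patient triggered at M3 is due a handgrip at that visit.
- M0 and M3 readings can carry an all-randomised analysis. Take 69 patients per arm, SD 8 kg, visit correlations of 0.80 to 0.85, and drop-out of under 20% that depends on the M3 change in opposite directions by arm. With a true effect of 2.00 kg, the completers' ANCOVA gave about 2.6 kg, and an analysis predicting M6 from M0 and M3 gave 1.99 kg.

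That last exercise also does not show that the estimate would be inflated by some 30%. It lets handgrip itself drive drop-out, whereas the triggers at issue in Table 2 are iPTH values.

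These points stand, and they limit the claim to a risk. They do not remove the arm-specific rules, which are explicit, or the completer-based target. Whether a patient is still measured is a conduct rule. An analysis plan can model M6 readings that were never taken, but it cannot recover them.

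**Conclusion.** The point holds as a risk that the stated rules create. The article applies opposite iPTH filters to the two arms after randomisation, counts its target in protocol completers, and makes no provision for an M6 handgrip after a trigger, while promising intention to treat.

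Whether the primary comparison is harmed depends on three things the article does not give: whether triggered patients are measured, how many there are, and how iPTH relates to grip change. Bias is zero if iPTH and grip change are unrelated. Under the assumptions in the working (5–15% removed per arm, correlation 0.2–0.3, SD 8 kg), it is about 0.35 to 1.3 kg against a design difference of 5 kg, and its direction is unknown. The sample size itself is correct, so the issue is bias and not power.

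**What to change.** 1. State that meeting a drop-out criterion does not end outcome follow-up. Measure handgrip at M3 and M6 in every randomised patient who is alive, consenting and able to grip. Handgrip is taken before dialysis sessions, so most patients with an iPTH trigger remain within reach.
2. Define the target either as patients with an M6 handgrip whatever treatment they received, or as a fixed number randomised, 110 / (1 − d) with d stated. Delete the condition about protocol completion. A fixed 110 randomised with no allowance would leave about 87%, 83% or 78% power (normal approximation) at 10%, 20% or 30% loss.
3. Analyse all randomised patients as allocated, using M0 and M3 handgrip where M6 is missing. Keep protocol completers as a sensitivity analysis.

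The cost is an amendment and a few extra handgrip readings. The article describes recruitment as still open, and M6 readings not taken cannot be recovered later. The clinical triggers, and what they mean for treatment, are for the sponsor to reconcile with the intention-to-treat statement. No clinical rule is proposed here.

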### Biological dosing

In order to facilitate patient recruitment and retention, biological analysis will be performed in the local usual hemodialysis center laboratories. As each center might have different dosing techniques, randomization will be stratified by center. Labs were asked to inform if any dosing technique was to change during the study regarding calcium, phosphate, iPTH, or 25OHD dosing.

Biological values will be performed every 3 months during the wash-out and treatment phase to search for drop-out criteria or the possibility to randomize patients.

### Randomization

Randomization will be centralized in the coordination center of the study, at Phocean Institute of Nephrology, Marseille, France. Patients will be randomly allocated to each arm (treatment or no treatment) in a 1:1 ratio between the two arms using a computerized random program (MINIM, program for randomizing patients to treatment groups in clinical trials by the method of minimization, by Stephen Evans, Simon Day and Patrick Royston) stratified per center, age (< or ≥ 70 years old) and gender. MINIM is a program for randomizing patients to treatment groups in clinical trials by the method of minimization. This software randomly assigns the first participants, then accounts for the covariates of participants (center, age, gender) previously enrolled, and assigns each new participant to the group that provides better balance.

### Statistical analysis

A flow-chart diagram will describe the number of patients by status (inclusion, drop-out, randomization, follow-up). Patient characteristics will be described by treatment groups: qualitative data will be expressed as number and percentages, and quantitative data as mean and 95% confidence interval. Comparison between the two groups will be performed using the Chi-2 test for qualitative variables and the Student test for quantitative variables. If conditions to use these tests are not met, comparisons will be performed using appropriate non-parametric tests (Fischer’s exact test, Mann-Whitney test). Analyses will be considered as significant if *p* value is ≤ 0.05, in a bilateral situation.

The main objective will be analyzed by comparing muscle strength variation during the treatment period (M0–M6) between treated (receiving cholecalciferol) and non-treated group using a covariance analysis in which principal analyzed effect will be the treatment group and will be included as covariables the initial muscle strength, the study center, age stratification (< or ≥ 70 years old), and gender. Principal analysis will be based on intention to treat principle.

Secondary analyses will compare the ADL, FIND, and KDQOL scores between the two treatment groups using the same statistical method (analysis of covariance). The decreased of 25OHD plasma level will be described at the end of the wash-out period (mean change from inclusion and number of patients with 25OHD ≤ 50 nmol/l). To analyze factors associated with 25OHD lowering speed, a linear (or the most appropriate function) mixed model (random intercept and/or slope) will be performed including variables potentially related to 25OHD changes, such as but not limited to age, gender, BMI, diabetes, and duration of previous 25OHD treatment.

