### Study intervention

Study protocol is described in Table 1. All patients of participating dialysis centers will be screened for inclusion and non-inclusion criteria. If every inclusion criterion is met, but no non-inclusion criterion, investigators will inform patients and collect their written informed consent.

**Table 1 Tab1:** Study procedures

	Screening	Inclusion	Wash-out phase	Treatment/no treatment (random phase)		
	V1	V2	V3 and/or V3bis and/or V3ter and/or V3quater	V4/M0	V5/M3	V6/M6
Check of selection criteria	✓					
Patient information	✓	✓				
Check of inclusion criteria		✓				
Consent Form Signature		✓				
Socio-demographic data		✓				
Clinical data		✓	✓	✓	✓	✓
Biological data		✓	✓	✓	✓	✓
Including 25OHD, iPTH, calcemia, phosphor		✓	✓	✓	✓	✓
Randomization				✓		
Dispensation treatment/no treatment				✓	✓	✓
Main criterion: handgrip		✓	✓	✓	✓	✓
Secondary criteria: ADL, FIND, KDQOL scores				✓	✓	✓
Compliance			✓	✓	✓	✓

During the wash-out period, all vitamin D supplementation (native or active) will be suspended. All other medical treatments and dialysis prescriptions will be maintained as usual care. 25OHD will be measured every 3 months as well as handgrip strength. If 25OHD lowers or equals to 50 nmol/L, the patient will be randomized. If not, the patient will continue wash-out for 3 additional months. After 12 months of washout, if 25OHD remains > 50 nmol/L, the patient will be excluded.

After randomization, muscle strength will be measured at baseline (at randomization) and 3 and 6 months. Variation of muscle strength at randomization and at the end of the study will be compared in the two groups.

During the treatment period, patients randomized in the cholecalciferol group will receive 100,000 UI oral cholecalciferol every month during 6 months, but no other vitamin D supplementation; patients randomized in the control group will receive no vitamin D at all. Medication will be provided to dialysis facilities; it will be given by the investigator at the end of dialysis session in the dialysis facility and the medication will be traced by the investigator. All other medical treatments and dialysis prescriptions will be maintained as usual care. Muscle strength will be measured at randomization, 3 and 6 months. Secondary judgment criteria will be measured at randomization and the end of the study. After 6 months with or without cholecalciferol supplementation, the study will end.

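### The primary ANCOVA of the M0–M6 handgrip change gives no role to the M3 handgrip, so patients lost after M3 contribute nothing unless M6 is imputed

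*Protocol article*

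**What the plan says.** All references are to the Methods of the protocol article.

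- **Schedule (Study intervention).** "After randomization, muscle strength will be measured at baseline (at randomization) and 3 and 6 months". Table 1 lists handgrip as the main criterion at M0, M3 and M6. It places the calcium and iPTH measurements at the same visits.
- **Comparison (Study intervention).** "Variation of muscle strength at randomization and at the end of the study will be compared in the two groups". The 3-month value is not mentioned.
- **Primary model (Statistical analysis).** "The main objective will be analyzed by comparing muscle strength variation during the treatment period (M0–M6", by analysis of covariance with treatment group as the main effect, in which "will be included as covariables the initial muscle strength, the study center, age stratification (< or ≥ 70 years old), and gender". There is no M3 term and no repeated-measures term.
- **Population (Statistical analysis).** "Principal analysis will be based on intention to treat principle". The article states no rule for a missing M6 value, neither exclusion nor imputation.
- **Loss (Table 2).** Drop-out criteria include death, transplantation, hypercalcemia and inability to perform handgrip. Two iPTH criteria differ by arm after randomization: high iPTH applies to the untreated group, low iPTH to patients receiving cholecalciferol.
- **Size (Study population and sample size).** The target effect is set by "To show a 5-kg difference between the two groups, considering a standard deviation of 8 kg". With 90% power at the 5% level, the article arrives at 54 per arm. Recruitment continues until 110 patients finish according to the protocol.

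**The concern.** An ANCOVA of change to a single time point can use a patient only if that time point is observed or imputed. Outcome, method and covariates are all named, and M3 is not among them. As written, a patient with M0 and M3 but no M6 does not inform the treatment effect, which sits awkwardly with the intention-to-treat statement.

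Two things are at stake. One is precision, because a reading already taken goes unused. The other is validity. If those who leave after M3 differ in grip course from those who stay, and differ in another way in each arm, an estimate from completers alone is biased. Recruiting more completers does not remove that bias. Patients dropped on their M3 biochemistry should normally have an M3 grip, since Table 1 puts both at one visit, so the information to correct for this often exists. The same section already plans a mixed model for the 25OHD decline during wash-out, so the method is not foreign to the team.

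**Working it through.** **1. The plan's own figure.** Inputs from the sample-size section: difference 5 kg, SD 8 kg, two-sided α 0.05, power 0.90.

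n per arm = 2 × (1.960 + 1.282)² × 8² / 5² = 2 × 10.51 × 2.56 ≈ 53.8, rounded up to **54**. This matches the plan; a t-based calculation gives 55. With 110 completers (55 per arm), power is 0.906 (normal) or 0.901 (t).

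**2. Precision gained from M3.** The documents give neither a drop-out rate nor a correlation. Assumed ranges: M6 missing 10–30%, equal correlation r between visits of 0.6–0.9, and 50–100% of those without M6 having an M3 value. Let n_c be patients per arm with M6, and n_3 those with M3.

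- Partial correlation of M3 and M6 given M0: p = (r − r²)/(1 − r²) = r/(1 + r).
- Complete-case variance: 2σ²(1 − r²)/n_c.
- Variance using M3: 2σ²(1 − r²)[(1 − p²)/n_c + p²/n_3].
- Ratio of the second to the first: (1 − p²) + p² × n_c/n_3.

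Example with 54 randomized per arm, r = 0.8, 20% without M6, all with M3: p = 0.8/1.8 = 0.444, p² = 0.198, n_c = 43.2, n_3 = 54. The ratio is 0.802 + 0.198 × 43.2/54 = 0.960, so the effective number is 43.2/0.960 = 45.0 per arm.

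Over the whole range, with 54 randomized per arm and the stated SD of 8 kg:

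| M6 missing | Completers per arm | Effective number with M3 | Power, completers only | Power with M3 |
|---|---|---|---|---|
| 10% | 48.6 | 49.0–49.7 | 0.869 | 0.871–0.876 |
| 20% | 43.2 | 43.9–45.2 | 0.828 | 0.833–0.844 |
| 30% | 37.8 | 38.8–40.5 | 0.776 | 0.786–0.803 |

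The variance falls by about 1–7%, worth 0.2 to 2.7 power points. These powers ignore the gain from baseline adjustment, which raises both columns.

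**3. Bias.** Large-sample simulation with SD 8 kg, r = 0.8 and half of the M6 effect present at M3. The logit of loss after M3 is −1.6 plus a slope (−0.3, 0 or +0.3) times the M0–M3 grip change.

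| Loss related to M0–M3 change | Loss, control / treated | True effect (kg) | Completers only (kg) | Using M3 (kg) |
|---|---|---|---|---|
| Not related | 17% / 17% | 0 | 0.01 | 0.01 |
| Not related | 17% / 17% | 5 | 5.00 | 5.00 |
| Same direction in both arms | 24% / 24% | 0 | 0.02 | 0.02 |
| Same direction in both arms | 24% / 15% | 5 | 4.83 | 5.01 |
| Control arm only | 24% / 17% | 0 | −0.53 | 0.01 |
| Control arm only | 24% / 17% | 5 | 4.46 | 5.00 |
| Opposite directions | 24% / 24% | 0 | −1.09 | 0.01 |
| Opposite directions | 24% / 36% | 5 | 3.65 | 5.00 |

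The errors with arm-dependent loss run from about 0.5 kg to 5 − 3.65 = 1.35 kg.

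A second set of runs shows that the sign is not fixed (69 per arm, between-visit correlations 0.80, 0.80 and 0.85, roughly 16–20% of M6 missing). Opposite-direction loss gave 3.0 kg for a true 2.0 kg and 1.1 kg for a true zero; control-only loss gave 1.47 kg for a true 2.0 kg. The likelihood estimate using M3 gave 2.0, 0.0 and 2.02 kg. With the same correlations, loss differing by arm (23% against 18%) but unrelated to grip gave 1.99–2.02 kg for a true 2.00 kg, and same-direction loss gave 1.96–2.00 kg.

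**The case against.** A reader might infer that the trial will discard every patient without M6, that the drop-out rules guarantee such losses, and that the result will therefore be biased. The documents do not support this.

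- **Exclusion is not written.** The article states intention to treat and is silent on missing values. Imputing M6, even from M3, would fit its wording. A condensed article commonly leaves that rule to the full protocol or analysis plan, so the silence is no fault in itself. What remains is that the model the article does specify has no place for M3.
- **M3 is not always in hand.** Patients lost before M3 have no such value. Nor does the article say that grip measurement stops when a drop-out criterion is met.
- **Precision is hardly at issue.** The gain is small, and recruiting to 110 completers protects the planned power. This stands in full.
- **The bias is assumed, not shown.** The arm-specific criteria concern iPTH, not grip; the one grip-related criterion applies to both arms. Different drop-out rates alone do not bias ANCOVA. Size and sign follow from the mechanism chosen. This also stands, and the kilogram figures are illustrations only.
- **The alternative has limits.** The M3-based model looks unbiased above because the simulated loss depends only on values in that model. Loss through death or iPTH need not.

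ANCOVA adjusted for baseline and the minimization factors is a sound method when M6 is complete. These points narrow the concern. They do not give a reason to leave the M3 reading out.

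**Conclusion.** The concern holds in a limited form. The stated primary analysis makes no use of a handgrip reading that the protocol collects, and without imputation patients lost after M3 drop out of an analysis labelled intention to treat. Table 2 makes some informative loss plausible, not certain.

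The cost in precision is about 1–7% of variance under the assumed ranges, with power still about 0.90 at 110 completers. The possible bias is roughly 0.5–1.35 kg, in either direction, against a 5-kg target. It arises only if loss depends on the M0–M3 grip change differently by arm. If loss is unrelated to grip, there is none. If the relation is the same in both arms, it is small: at most 0.17 kg in the runs shown. The drop-out rate, correlations and loss mechanism are all assumptions. This is a worthwhile improvement to the method; it does not show that the trial's result will be wrong.

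**What to change.** Make the primary analysis a repeated-measures model of M3 and M6 handgrip in all randomized patients with at least one post-baseline value. Terms: arm by visit, baseline grip by visit, centre, age group and gender, with unstructured covariance between visits. Keep the M6 arm difference as the single primary contrast, so the question and the multiplicity position do not change. Report the planned ANCOVA as a sensitivity analysis; with complete data the two give essentially the same answer.

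The cost is about a paragraph of analysis text and slightly more modelling, with no new visits or data. The text should state the limits: validity still requires that loss depends only on observed data, and patients lost before M3 are not recovered.
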